
### Statistical considerations

The case-cohort design was selected to balance statistical power, feasibility, and cost in a large, globally distributed pregnancy cohort. Full multi-omic profiling of all participants is neither economically nor logistically feasible, particularly for low-prevalence outcomes such as stillbirth and PE. The case-cohort framework enables comprehensive inclusion of all cases for each adverse pregnancy outcome while sampling a representative sub-cohort from the full population. This preserves the ability to estimate population-level risks and outcome prevalence, while substantially reducing assay volume and cost. This design also supports both outcome-specific analyses and integrative cross-outcome comparisons through the use of a shared reference sub-cohort. It retains the inferential strengths of a prospective cohort, while enabling deep molecular characterisation of rare and clinically important phenotypes. When integrating molecular and clinical data into cohort-level analyses, we will apply established case-cohort weighting and variance estimation methods (*e.g.* Prentice-weighted Cox models and survey-weighted regression frameworks) to ensure unbiased population-level inference and correct standard errors.

Nested case-control sampling is used for targeted assays and discovery-oriented analyses where relative contrasts between cases and matched controls are most informative and cost-efficient. These analyses will be interpreted as conditional, outcome-specific comparisons and will not be pooled directly with population-level estimates derived from the case-cohort framework. Where results from nested case-control analyses inform broader models, they will be re-estimated within the weighted case-cohort structure to preserve representativeness and avoid selection bias.

### Statistical power

For high-dimensional, regularised machine-learning models operating across multiple molecular modalities, classical closed-form power calculations are not available. Instead, effective power is governed by the number of outcome events, feature dimensionality, and the cross-validation and regularisation strategy. The MOMI substantially exceeds the scale of prior pregnancy multi-omics studies, including those that have successfully identified reproducible molecular signatures of PE and PTB [17,19,20]. The inclusion of all cases for each adverse outcome, coupled with a large, representative sub-cohort, maximises event density and information content, while maintaining cohort-level validity.

## DATA HARMONISATION

The Consortium has developed a harmonised framework for sociodemographic, clinical, and phenotypic variables across the biorepository sites. Specifically, SAS/STATA programmes were developed for harmonising site-specific data sets and quality control programmes for ensuring data consistency, while all harmonised datasets will be uploaded to a centralised platform. The biorepository sites upload clinical and phenotypic metadata that can be accessed by the analytical partners, who, conversely, upload their respective analytical data for cohort investigators. Although the GARBH-INi data, in compliance with government regulations in India and the GARBH-INi funding structure, are controlled by their team, data and analyses pipelines have been harmonised with the overarching MOMI Consortium. A first critical step was the harmonisation of birth outcome data, first on a site-specific level and then through central adjudication for confirmation.

PTB was defined as babies born alive before 37 weeks of pregnancy are completed [32]. Three subcategories were defined based on the GA: extremely preterm (<28 weeks, 0 days GA), (very preterm (28 weeks, 0 days to 31 weeks, 6 days GA), and moderate to late preterm (32 weeks, 0 days to 36 weeks, 6 days GA). The GA assessment was based on the Hadlock formula, which was implementable across all sites; missing head circumference data at AMANHI sites prevented the implementation of INTERGROWTH-21st formula. At time points with available ultrasound data, the GA was computed using either crown rump length or a composite of femur length and biparietal diameter. For the purpose of this study, preterm stillbirths will be evaluated as a part of SB outcomes.

SGA was defined based on the INTERGROWTH-21st standards [33] using the 10th percentile as cut-off. Only some cohort sites were able to define fifth or third percentile SGA babies. Due to discrepancies in the measurement of birth weight among the different cohort sites, birthweights were coded as level 1 or 2 when birthweights were measured within 48 or 72 hours of delivery, respectively, and as level 3 when measured at three days or later.

SB was defined as delivery of a foetus at or after 22 weeks of gestation with no signs of life upon delivery. Among total SB cases, we classified early SB as birth prior to or at 22 weeks, 0 days to 27 weeks, 6 days of GA, and late SB when it occurred at 28 weeks, 0 days GA or later. Otherwise, SB of PTB babies were included in SB case numbers. Clinical data were used to adjudicate antepartum SB (Figure S2 in the **Online Supplementary Document**). Antepartum SB was considered priority 1 when cardiotocographic or ultrasound data of foetal death before onset of labour or rupture of membranes were available. Evidence of maceration, mummification, or other signs of putrefaction of the stillborn foetus was ascribed as priority 2 antepartum SB. An absence of perceived foetal movements as reported by the mother before the onset of labour or rupture of membranes was termed priority 3 antepartum SB.

PE harmonisation was the most complex adjudication process (Figure S3 in the **Online Supplementary Document**). Because pre-pregnancy BP measurements and antihypertensive histories were not systematically available across sites, chronic hypertension could not be uniformly excluded at enrolment. To preserve phenotype specificity under these constraints, PE classification relied on a conservative adjudication framework incorporating evidence beyond elevated BP alone, incorporating maternal end organ dysfunction, proteinuria, and foetal growth restriction occurring after 20 weeks’ gestation. Women with BP 140 mmHg systolic or 90 mmHg diastolic at least four hours apart or at two visits and accompanied by proteinuria at the time of assessment were classified as PE. Women with severe BPs (BP 160 mmHg systolic or 110 mmHg diastolic) were classified as PE regardless of proteinuria. Women with proteinuria documented at a visit not coinciding with elevated BP were classified as PE if urinary tract infection was not suspected and end organ dysfunction was present. Maternal end organ dysfunctions considered for PE diagnosis include haematological dysfunction (*e.g.* thrombocytopenia), renal insufficiency, impaired liver function, pulmonary oedema, cerebral/visual symptoms (*e.g.* headaches, scotomata), and ultrasound-based diagnosed foetal growth restriction or birth weight <3 percentile based on GA. In the absence of proteinuria, women with non-severe BP and documented chronic pre-existing hypertension <20 weeks GA were excluded as PE cases. Women without proteinuria were classified as PE if they had severe BP (>160 mm systolic and/or >110 mm diastolic), without consideration of pre-existing hypertension status; had no pre-existing hypertension <20 weeks but presented with indications of end organ dysfunction >20 weeks; or experienced seizure >20 weeks without history of epilepsy (eclampsia). Based on these criteria, four categories of PE cases were defined, ranging from priority 1 (highest confidence) to priority 3 (lowest confidence), with remaining cases classified as non-PE. Once PE cases were confirmed by central adjudication, priority 1 and 2 PE cases were further stratified into early-onset PE and late-onset PE. The former was defined as PE developing before 34 weeks 6 days GA, and the latter as PE developing at or after 35 weeks.

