We hypothesise that the integration of data from multiple omics technologies will provide the means to define biological pathways that are altered in pregnant women with APOs and that, despite some overlap, unique signatures for PTB, PE, stillbirth, and SGA can be deduced to develop novel risk assessment tools and interventions. The inherent heterogeneity across the cohorts in different geographical locations will be counterbalanced by the tightly coordinated study design, data harmonisation, and adjudication of birth outcomes, and the extensively validated computational pipeline developed in prior studies [15-21]. Furthermore, only APO signatures that are reproducible across different cohort sites will be considered biologically and clinically meaningful. This protocol presents the objectives, study design, and analytical approaches of the MOMI Consortium and outlines how integration of multi-omics and metadata will enhance the understanding of pregnancy biology, inform risk prediction models, and contribute to the development of targeted interventions to improve maternal and infant health.

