### Sociodemographic and clinical data

Sociodemographic data (age, partner status, education, tobacco, alcohol and drug use), weight, medical history, parity status and, in case of prior pregnancy, pregnancy history and outcome, were documented at enrolment. A medical exam was conducted at the same time point that included body mass index, blood pressure (BP), and haemoglobin measurement, urine analysis, testing for HIV and other sexually transmitted diseases, assessment of pregnancy symptoms, and a dating ultrasound. Subsequent antenatal visits included determination of GA, recording of pregnancy symptoms since the prior visit, and testing for urine, haemoglobin, BP, heart rate, and weight. At delivery, medical conditions or medications during pregnancy and/or delivery, time of membrane rupture, delivery time, and birth outcome were documented. The foetus’s heart rate and fundal height were also assessed. Data also captured indications for provider-initiated delivery or caesarean section, postpartum complications, neonatal vital status, and Apgar score. Women and infants were seen at least once between six weeks to six months post-delivery. The infant was evaluated for any diseases and medications since birth, and evaluated for infant weight, head circumference, mid-upper arm circumference, temperature, heart and respiratory rates. The mother underwent a pelvic exam and was assessed for weight, BP, heart rate, temperature, and oedema.

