Due to the high cost-per-sample and medium/low sample throughput, a case-cohort study design categorised into the sub-cohort and nested case control study (**Figure 3**) was selected. The sub-cohort includes the longitudinal samples of approximately 30% of pregnant women in the full cohort and available cord blood samples for group I nutrient analysis (Figure S8 in the **Online Supplementary Document**). Nutrients of this group include vitamin A, D, E, folate, B12, total homocysteine, ferritin, transferrin receptor, iodine, minerals (copper, selenium, magnesium, calcium, phosphorus, iron, potassium, sodium), alpha-1-acid-glycoprotein, C-reactive protein, high-density lipoprotein, low-density lipoprotein, and triglycerides. It is noteworthy that the Group I Nutrient analyses will be performed by the icddr,b, representing the only in-country analysis. Group II nutrients (vitamins B1, B2, B3, B5, B6, B7, choline, and a targeted metabolomics panel) will be analysed in the longitudinal samples of PE, SB, and vPTB cases and their matched term controls (1:3 ratio). The B vitamins, choline and related metabolites will be measured by ultra-high performance liquid chromatography (UHPLC)- MS/MS and fatty acids and amino acids by UHPLC-MS/MS – MxP®Quant 500 XL kit [51,54].

As specimens of the GARBH-INi cohort will be analysed by the Translational Health Science and Technology Institute, India (THSTI), a harmonisation plan between THSTI and icddr,b, or between THSTI and UC Davis for nutrient group I or group II analyses, respectively, was developed. Institutions will apply standardised test methods, instrument calibration, quality control measures, external quality assurance schemes, and reporting methods. The joint analysis of the nutrient group I and II parameters from the GAPPS, AMANHI and GARBH-INi sites will allow for validation across sites and analytical platforms.

The placenta tissue analysis will be particularly valuable towards the goal of designing novel diagnostics or intervention strategies to prevent APOs, as several of the APOs are either entirely or partially attributable to placental dysfunction. These include early-onset PE, foetal growth restriction, and a subset of PTB cases. Since the placenta is in direct contact with maternal blood, placental APO signatures will likely be highly complementary to APO signatures in maternal blood and provide crucial information on the involvement of certain biological pathways.

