## DATA ANALYSIS AND DATA INTEGRATION

The analytical objectives of MOMI are to determine the omics signatures of each week of advancing GA (*i.e.* temporal pregnancy progression), the strength of association of each omics or other analytical platform with each APO through machine learning modelling (thereby identifying unique features of each APO phenotype), and how site-specific effects can be used to inform model generalisation. Analysis will proceed systematically from using risk signatures derived from a single platform to signatures identified through integration of multiple omics risk signatures, and from individual cohorts to cross-cohort integration. The integration of phenotypic metadata, including sociodemographics and clinical variables, will further enhance the understanding of biological mechanisms underlying APOs and improve prediction of APOs.

The structural heterogeneity across global cohorts presents a central analytical challenge that will be addressed by explicit methodological safeguards against batch effects, missingness, site heterogeneity, and overfitting. The MOMI analytical framework is built on a mature and extensively validated computational pipeline developed and applied across multiple large, multi-site pregnancy cohorts, including prior MOMI studies [17,19] and in subsequent multi-omic integration and machine-learning frameworks [15,18,20,21]. In these works, we have implemented harmonised preprocessing and quality control, explicit modelling of batch and site effects, and integration strategies that preserve biological signal while mitigating technical variation (*e.g.* empirical Bayes and factor-based normalisation, network-based integration, and multi-view latent variable models). Missing data are handled through a combination of modality-aware imputation and model architectures that accommodate partially observed samples, enabling inclusion of participants with incomplete data without introducing bias.

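### Preterm birth is classified by gestational age only, so live births initiated early for preeclampsia or growth restriction count as PTB cases and blur the PTB-specific signature the study seeks

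*Protocol article*

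**What the plan says.** The section Data harmonisation gives the case definition: "PTB was defined as babies born alive before 37 weeks of pregnancy are completed". It then says "Three subcategories were defined based on the GA" (extremely, very, and moderate to late preterm). The only group moved elsewhere is foetal deaths: "preterm stillbirths will be evaluated as a part of SB outcomes". How labour began plays no part.

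The relevant information was collected. Under Sociodemographic and clinical data the article says "Data also captured indications for provider-initiated delivery or caesarean section", and it lists time of membrane rupture among the delivery variables. Stillbirth adjudication, in Data harmonisation, refers to onset of labour and rupture of membranes. PE is graded by confidence and split by onset. No comparable step is described for PTB.

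The aim is separation of outcomes. The introduction hypothesises that "despite some overlap, unique signatures for PTB, PE, stillbirth, and SGA can be deduced". Data analysis and data integration sets out to measure each platform's association with each outcome, "thereby identifying unique features of each APO phenotype". The Discussion expects signatures specific to a given outcome. The placental paragraph of Analytical studies lists outcomes wholly or partly due to placental dysfunction: "These include early-onset PE, foetal growth restriction, and a subset of PTB cases".

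**The concern.** The definitions of PTB, PE and SGA are not mutually exclusive, and the article states no hierarchy or exclusion for women who meet more than one. A pregnancy ended early because of PE or poor growth enters the PTB case group because of another outcome under study. Three consequences follow.

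- **Specificity.** A PTB model can partly learn PE or growth-restriction biology. A feature then reported as belonging to PTB may not.
- **Dilution.** A marker of spontaneous preterm labour is averaged with births in which it may play no role.
- **Transport.** Only findings that replicate across sites will be interpreted as biologically meaningful. If the mix of spontaneous and provider-initiated births differs by site, a real marker of spontaneous PTB may fail in a held-out site and be discarded.

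The small placental comparisons have the least room for a mixed case group: 26 PTB cases for bulk transcriptomics and 15 for single-nuclei sequencing.

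**Working it through.** **1. Reproducing Table 2.** PTB: 1587/16 221 = 9.78%, as stated. Total adverse outcomes: 1587 + 290 + 3527 + 168 = 5572, and 5572/16 221 = 34.35%, as stated. The total is the plain sum of the four outcome rows, so the table does not show how many women have more than one outcome.

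**2. How much of PTB could be PE?** The documents give no cross-tabulation. The ceiling assumes that every PE case in Table 2 delivered live and preterm (PE/PTB). A smaller scenario assumes that only the early-onset PE cases did (early-onset PE/PTB).

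| Site | PTB | Early-onset PE | All PE | Scenario | Ceiling |
|---|---|---|---|---|---|
| Zambia | 223 | 35 | 85 | 15.7% | 38.1% |
| GAPPS Bangladesh | 384 | 7 | 35 | 1.8% | 9.1% |
| AMANHI Bangladesh | 366 | 3 | 7 | 0.8% | 1.9% |
| Pakistan | 372 | 9 | 39 | 2.4% | 10.5% |
| Tanzania | 242 | 22 | 124 | 9.1% | 51.2% |
| Combined | 1587 | 76 | 290 | 4.8% | 18.3% |
| GARBH-INi | 764 | 13 | 166 | 1.7% | 21.7% |

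The scenario column is not a strict lower bound, because the text defines early onset by when PE develops and some of these pregnancies may have ended in stillbirth. Neither column counts provider-initiated births. Some women with PE labour spontaneously, and deliveries initiated for other reasons are not included.

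**3. SGA within PTB.** If SGA were independent of PTB (an assumption), 1587 × 3527/16 221 ≈ 345 PTB cases would also be SGA below the 10th percentile, and 1587 × 1551/16 221 ≈ 152 below the 3rd.

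**4. Dilution.** Let p be the provider-initiated share of PTB. The documents give no value, so 15–35% is assumed. Suppose a marker differs by 0.30 SD in spontaneous PTB and by 0 in provider-initiated PTB. The pooled effect is 0.30 × (1 − p).

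**5. Net gain from restriction.** Controls are the 16 221 − 1587 = 14 634 women without PTB. Information is the squared effect divided by (1/cases + 1/controls). Spontaneous-only relative to pooled is

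(1/1587 + 1/14 634) / { (1 − p)² × [1/(1587(1 − p)) + 1/14 634] }.

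| p | Provider-initiated cases | Pooled effect | Spontaneous cases | Net gain |
|---|---|---|---|---|
| 0.15 | 238 | 0.255 SD | 1349 | 1.19 |
| 0.25 | 397 | 0.225 SD | 1190 | 1.37 |
| 0.35 | 555 | 0.195 SD | 1032 | 1.59 |

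**6. Does it threaten detection?** Across the full cohort, no. At p = 0.35 the pooled z is 0.195/√(1/1587 + 1/14 634) = 7.4. Within one site the margin is thinner. Tanzania has 242 PTB cases and 4501 − 242 = 4259 others, so z = 0.195/√(1/242 + 1/4259) = 2.95.

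**The case against.** The strongest reply has four parts.

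- **The hypothesis allows for overlap.** It does, in the words just before the claim of unique signatures. A reader might infer that the PTB definition contradicts the hypothesis, but the documents do not support that. They show that the signature is exposed to mixing, not how strongly it is affected.
- **A condensed article may leave sub-phenotypes to the full plan.** This is fair for sensitivity analyses in general, and recording the indication is compatible with a later split. Here, however, the case definition and its subcategories are themselves stated, and they rest on gestational age alone.
- **Site safeguards exist.** Hold-out validation, site terms in the models and pathway analysis by site make a false universal signature less likely. They do not protect a true marker of spontaneous PTB, which can fail replication when case mix differs. They also do not remove a PE or growth-restriction signal that is present at every site.
- **All-cause PTB is a legitimate target for risk prediction.** This stands. Making spontaneous PTB the sole primary phenotype would change the question and would not correct an error.

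Two further limits stand. The article gives no completeness figures by site for the indication variable. It also reports that other key variables were unavailable at some sites, such as head circumference and pre-pregnancy blood pressure.

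**Conclusion.** The point holds as a weakness in a stated case definition. As published, nothing separates live preterm births initiated for PE or growth restriction from spontaneous ones, although relevant data were recorded and outcome-specific signatures are the aim.

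The size cannot be fixed from the documents. PE as counted in Table 2 is at most 18.3% of pooled PTB, and the wide spread of site ceilings leaves room for different case mixes. A reader might take the Tanzanian 51.2% as an estimate. It is only a bound, under the extreme assumption that all PE cases there delivered live and preterm.

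The dilution to 0.26–0.20 SD rests on the assumed 15–35% share and on a marker that is wholly null in provider-initiated births. A partial effect there would shrink the loss. A reader might also compute 1/(1 − p)², or 1.4- to 2.4-fold, as the gain in sample size. That compares equal case numbers and ignores the cases lost by restriction. The net gain is about 1.2- to 1.6-fold.

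**What to change.** 1. Where the recorded indication and membrane-rupture data allow, derive spontaneous and provider-initiated PTB at each site, under one harmonised rule.
2. Prespecify association and prediction models for each, alongside all PTB. All PTB remains a valid target for overall risk prediction.
3. Call a signature PTB-specific only if it holds in spontaneous PTB or, where onset cannot be classified, in PTB without PE or SGA.
4. Report by site the overlap of PTB, PE and SGA and the number of unclassifiable deliveries. These counts would show how large the problem is and help in reading a failed cross-site replication.

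No new assays are needed, and site-specific and cohort-wide analysis is still under way. The costs are fewer cases per sub-phenotype (most felt in the placental subsets and the smaller sites), some deliveries that cannot be classified, and a little more analysis work.

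### The severe-BP route to preeclampsia is worded two ways at its cut-off and, as printed, rests on blood pressure alone, contrary to the framework's stated principle

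*Protocol article*

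**What the plan says.** The Data harmonisation section of the protocol article describes several routes by which a woman becomes a preeclampsia (PE) case.

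- **Non-severe route:** "Women with BP 140 mmHg systolic or 90 mmHg diastolic at least four hours apart or at two visits and accompanied by proteinuria". This needs both a repeat and a second sign.
- **Severe route, first statement:** "Women with severe BPs (BP 160 mmHg systolic or 110 mmHg diastolic) were classified as PE regardless of proteinuria". No comparison sign stands before 160 or 110, and no repeat is mentioned.
- **Severe route, second statement, for women without proteinuria:** "classified as PE if they had severe BP (>160 mm systolic and/or >110 mm diastolic), without consideration of pre-existing hypertension status". Here the sign is strictly greater-than. Again no repeat is mentioned.
- **End-organ route without proteinuria:** women who "had no pre-existing hypertension <20 weeks but presented with indications of end organ dysfunction >20 weeks".
- **Exclusion without proteinuria:** "women with non-severe BP and documented chronic pre-existing hypertension <20 weeks GA were excluded as PE cases". This applies to non-severe readings only.

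The paragraph introduces these rules as a "conservative adjudication framework incorporating evidence beyond elevated BP alone", needed because chronic hypertension could not be ruled out uniformly at enrolment. It refers to Figure S3 for the process, then mentions priority tiers 1 to 3 and central adjudication. The Discussion relies on this framework to argue that high-confidence cases are probably not chronic hypertension on its own, and that any remaining misclassification pulls associations towards the null.

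**The concern.** There are two linked problems.

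First, the severe cut-off is printed in two forms that part company at the boundary value. Readings of exactly 160 or 110 are common wherever values are rounded, so the boundary is not a purely theoretical case.

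Second, the route that needs no other evidence is also the one for which no confirmation is stated. The non-severe route asks for readings "at least four hours apart or at two visits and accompanied by proteinuria". The severe route, as printed, asks for no repeat, no proteinuria and no end-organ sign, and sets pre-existing hypertension aside. This is BP alone, which the framework says it goes beyond. It is also the route by which a woman with chronic hypertension and no other sign of PE could enter the case set.

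At stake is the specificity of a rare phenotype. PE signatures are to be interpreted only if they replicate across sites, and one site contributes only 7 cases, so a few doubtful cases can matter.

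**Working it through.** **1. The stated PE count reproduces.** Table 2 gives 85 + 35 + 7 + 39 + 124 = 290 cases, and 290 / 16 221 = 1.79%, as printed. No stated figure is shown to be wrong.

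**2. The cut-off sentences side by side.** Take a woman without proteinuria, end-organ sign or seizure, whose highest reading is exactly 160 systolic or exactly 110 diastolic, with the other value below its cut-off.

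- First sentence, read as reaching 160 or 110: a case.
- Second sentence, strictly above: not severe, so not a case by this route. If she has documented hypertension before 20 weeks, the non-severe exclusion removes her explicitly.
- If the missing sign in the first sentence was also strictly greater-than, the two agree and only an unclear print remains.

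The greater-than sign prints intact elsewhere in the paragraph. A lost symbol was therefore more probably at-or-above, which makes a real difference at the boundary the likelier reading. The 140/90 sentence also lacks a sign, which fits a symbol lost in extraction.

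A woman with end-organ dysfunction after 20 weeks and no earlier hypertension is a case under either sentence. The boundary matters only for women with no other route.

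**3. The principle against the route.** The principle is evidence beyond elevated BP. The severe route has severe BP as its only condition, with proteinuria and hypertension history both waived. The two cannot both hold for cases admitted by this route alone.

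**4. Do the tiers settle it?** The text stratifies only priority 1 and 2 cases by onset. In Table 2, early onset sums to 35 + 7 + 3 + 9 + 22 = 76 and late onset to 50 + 28 + 4 + 30 + 100 = 212. Together these make 288, and the footnote accounts for 2 more through missing gestational age, giving 290. Either all 290 are priority 1 or 2, or priority 3 cases were stratified contrary to the text. The article does not say which tier a BP-only case receives.

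**5. Illustration only: why a repeat rule would matter.** The documents give no measurement SD. Assume a constant true systolic BP T, independent normal readings, a within-person SD s of 8 to 12 mmHg, and k = 4 or 5 readings. Then p = 1 − Φ((159.5 − T)/s), the chance of at least one reading of 160 or more is 1 − (1 − p)^k, and the chance of at least two is 1 − (1 − p)^k − k·p·(1 − p)^(k−1).

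- T = 140, s = 10, k = 4: p = 0.0256, at least one 9.9%, at least two 0.4%.
- T = 140, full range: 3% to 23% against 0.03% to 2.4%.
- T = 150, full range: 39% to 70% against 7% to 29%.

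**6. Illustration only: how often the boundary value occurs.** Assume systolic readings with mean 112 to 120 and SD 12 to 15, recorded to the nearest g mmHg. The share of readings at or above 160 that equal exactly 160 is P(160 ± g/2) / P(≥ 160 − g/2). It is 18% to 30% for g = 1 and 33% to 51% for g = 2, and higher with coarser rounding. These are shares of readings, not of women.

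**7. What cannot be computed.** The documents do not say how many of the 290 cases entered by severe BP only, on one reading, or at exactly 160 or 110. No corrected PE count can be derived.

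**The case against.** The strongest reply is that much of this depends on material the reader cannot see. The absent sign may be an extraction loss, the article condenses a fuller document, and the algorithm is in Figure S3. The first sentence speaks of severe BPs in the plural, which could imply more than one reading. Tiers and central adjudication follow, and an isolated severe reading may already sit in the lowest tier. The route is also an explicit exception, stated twice, and not an oversight.

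Much of this stands, and it rules out several stronger readings.

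- *One reading was enough to make a case.* A reader might infer this, but silence in a condensed article does not establish it.
- *Measurement noise determines who is a case.* The probabilities above describe a hypothetical woman under assumed inputs. They say nothing about how many of the 290 are affected.
- *Visit intensity drives the differences in PE frequency between sites.* The three AMANHI sites share one printed visit schedule, yet their PE frequencies are 0.23%, 1.56% and 2.75%, about a twelve-fold range (2.75 / 0.23 ≈ 12). Visit count is not the main driver.

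The reply does not remove the disagreement between the printed sentences and the stated principle. A deliberate exception still contradicts a claim that classification rests on more than BP. Nothing in the article tells the reader that BP-only cases lie outside the high-confidence tiers.

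**Conclusion.** The point holds as an inconsistency in a case definition. The severe cut-off is ambiguous, and probably conflicting, at exactly 160 or 110. As printed, the route also admits cases on BP alone with no stated repeat and without regard to earlier hypertension. This contradicts the declared principle and leaves the Discussion's statement about chronic hypertension without full support.

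The size is unknown. It is limited to women who qualify by no other route, and their number among the 290 is not given. The boundary conflict assumes that the first sentence means at or above. The point about the Discussion assumes that BP-only cases can reach priority 1 or 2, which the article neither confirms nor rules out. A reader might go further and call for a new repeat rule and full re-adjudication. The documents do not show that this is needed, and it would not clearly be cheap: PE status feeds the sub-cohort and the 1:3 case-control selection, and specimens are already being analysed.

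**What to change.** 1. Reconcile the two severe-BP sentences, the stated principle and Figure S3, so that one cut-off with its comparison sign and one repeat rule apply throughout. Which cut-off and which rule is for the consortium to decide.
2. Flag every case that qualifies by severe BP only, report the number by site, and state which priority tier these cases enter.
3. Repeat the main PE analyses without them as a sensitivity analysis, with particular attention to those with a single severe reading or with pre-existing hypertension. Leave sampling and weights unchanged.
4. If such cases are found in priority 1 or 2, qualify the Discussion's statement that high-confidence cases are unlikely to be chronic hypertension alone.

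The cost is a wording change, a flag built from BP values already recorded, and one extra set of analyses. The downside is slightly fewer PE cases, and so lower precision, in the sensitivity analysis.
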